## Abstract

**Background:**

Reducing blood pressure fluctuations during surgery is a key objective in improving patient outcomes. Although acupuncture has been suggested as a potential noninvasive intervention for blood pressure modulation, its effectiveness in reducing intraoperative fluctuations remains unclear.

**Objective:**

This study aims to investigate whether acupuncture can help stabilize blood pressure during surgery, particularly in women undergoing laparoscopic hysterectomy, a procedure known to cause marked hemodynamic changes during the early intraoperative phase.

**Methods:**

This is a prospective, single-center, randomized controlled clinical trial with a parallel-group design. Forty-eight adult patients scheduled to undergo a total laparoscopic hysterectomy are eligible for this study. Participants who provide consent will be randomly assigned in a 1:1 ratio to the acupuncture or placebo groups. They will be followed up for at least 14 days to assess the safety of the intervention, general anesthesia, and surgery. Researchers will compare the difference between the highest and lowest mean blood pressures from anesthesia induction to the postincision period as the primary endpoint. As secondary outcomes, systolic, diastolic, and mean blood pressures will be compared at each predetermined timepoint. The incidences of hypotension, hypertension, tachycardia, and bradycardia will be determined separately. The use of remifentanil at the early stage of surgery, rate of surgical discontinuation, and length of hospital stay will be assessed as surrogate indicators of stable general anesthesia and surgical procedures. For patient-reported outcomes, the Spielberger State-Trait Anxiety Inventory and EQ-5D-5L will be used to evaluate changes in anxiety and overall quality of life. This study may support the use of acupuncture as a complementary intervention to help maintain hemodynamic stability during laparoscopic hysterectomy. The study will be conducted in accordance with the Declaration of Helsinki and has been approved by the Institutional Review Board of CHA Ilsan Medical Center (ICHA 2022-11-010; date of approval: January 03, 2023).

**Results:**

Recruitment began in October 2023 and is expected to continue until December 2025. The intervention and data collection procedures are proceeding without major difficulties, with a dropout rate of 11.4%. As of June 2025, a total of 35 participants have been successfully recruited and randomized. Final data analysis is scheduled for completion by March 2026, and the study results are expected to be published in December 2026.

**Conclusions:**

This trial will provide valuable evidence on the efficacy of acupuncture for stabilizing intraoperative blood pressure and supporting hemodynamic control during laparoscopic hysterectomy.

**Trial Registration:**

ClinicalTrials.gov NCT05720884; https://clinicaltrials.gov/study/NCT05720884

**International Registered Report Identifier (IRRID):**

DERR1-10.2196/77009

## Introduction

Various factors, such as the use of agents that induce anesthesia, surgery-induced stress, and hemorrhage, contribute to blood pressure fluctuations during surgery. Because blood pressure values lower or higher than the normal range can affect a patient’s prognosis, reducing blood pressure fluctuations during surgery is an important goal for anesthesiologists [1,2]. A previous study reported that both hypotension and hypertension increased the oxygen demand in peripheral organs, postoperative complications, and mortality [3].

Blood pressure fluctuations that occur during anesthesia induction, tracheal intubation, and the early stages of surgery can develop rapidly within a short time due to the dynamic balance between anesthetic administration and noxious surgical stimuli. Hypotension may result from excessive analgesic or anesthetic dosing, while hypertension may arise from insufficient depth of anesthesia or sudden intense stimulation. Therefore, it is essential to anticipate the timing and intensity of such stimuli and preemptively titrate the concentration of analgesic agents to maintain hemodynamic stability. To minimize these abrupt hemodynamic changes, anesthesiologists and surgeons must perform thorough preoperative evaluations and develop individualized anesthetic plans tailored to the surgical context and patient condition [4-6].

Acupuncture is an established adjunctive therapy in anesthetic practice. Numerous studies have demonstrated that it can reduce the required doses of anesthetic and opioid agents, and alleviate postoperative symptoms such as pain, ileus, nausea, and vomiting [7]. These effects are thought to be mediated through modulation of the autonomic nervous system and nociceptive pathways, ultimately contributing to greater physiological stability throughout the perioperative period. However, despite these established effects, the role of acupuncture in directly modulating intraoperative blood pressure remains unexplored. The few available studies have primarily addressed either essential hypertension or the prevention of anesthesia-related hypotension as isolated conditions [8,9].

Notably, acupuncture has demonstrated bidirectional regulatory potential, with the capability of lowering elevated blood pressure and elevating suppressed blood pressure depending on the physiological context [10-13]. This dual effect suggests that acupuncture may serve as a stabilizing intervention for both extremes of hemodynamic instability under general anesthesia.

To investigate this, the study group designed a randomized controlled clinical trial to assess the impact of acupuncture on blood pressure fluctuations in patients undergoing total laparoscopic hysterectomy, a gynecological procedure known to cause significant hemodynamic shifts during the early intraoperative phase [14,15]. The study group hypothesized that acupuncture may contribute to overall blood pressure stability by attenuating both hypertensive and hypotensive responses in this highly dynamic setting.

## Methods

### Study Design

This is a prospective, single-center, randomized controlled clinical trial with a parallel-group design for blood pressure fluctuations during general anesthesia. Forty-eight adult patients scheduled to undergo a total laparoscopic hysterectomy will be included in this study. Participants who voluntarily consent to participate in the clinical trial will be randomly assigned in a 1:1 ratio to the acupuncture or placebo group. Eligible participants will be followed up for at least 14 days to assess the safety of the intervention, general anesthesia, and surgery.

The study protocol adheres to both the SPIRIT (Standard Protocol Items: Recommendations for Interventional Trials) guidelines (Multimedia Appendix 1) and STRICTA (Standards for Reporting Interventions in Clinical Trials of Acupuncture) guidelines (Multimedia Appendix 2). All study procedures will be performed in accordance with the Declaration of Helsinki and Korean Good Clinical Practice Guidelines. The study protocol has been registered and updated at ClinicalTrials.gov (NCT05720884), the Clinical Research Information Service, and the South Korean registration service for clinical trials (KCT0009149). This article describes the study based on protocol version 1.4 (dated November 13, 2024). The latest protocol will be updated in a timely manner for both registration sites.

### Ethical Considerations

The study protocol has been approved by the Institutional Review Board of CHA Ilsan Medical Center (ICHA 2022-11-010; date of approval: January 03, 2023). Written informed consent will be obtained from all participants after a thorough explanation of the study’s purpose and procedures, and after confirming their voluntary willingness to participate. To protect personal information, all data will be anonymized and stored using initials. Participants will receive a total compensation of 60,000 KRW (approximately US $45) for their time and involvement. Their participation may contribute to reducing perioperative blood pressure fluctuations for the broader public benefit.

This clinical study involves a data and safety monitoring board (DSMB) consisting of at least one medical clinician and a statistician. The composition and operation of the DSMB will be in accordance with the standard operating procedures of the trial. Study monitoring is scheduled to be conducted once a year. If a protocol modification is recommended, an appropriate amendment or response will be provided. If a suspected unexpected serious adverse reaction case occurs or the DSMB suspects a significant harmful association with the intervention and requests unblinding, the intervention researcher will unblind the allocation to other researchers and the committee, and submit the unblinded interim results.

### Eligibility

Participants scheduled to undergo surgical removal of the uterus for uterine fibroids and those who have an expected date of total laparoscopic hysterectomy by a gynecologist are eligible. The specific inclusion criteria are as follows: (1) age between 19 and 69 years, (2) American Society of Anesthesiologists (ASA) class I or II, (3) requirement for surgical removal of the uterus by a gynecology specialist, and (4) scheduled to undergo total laparoscopic hysterectomy in advance. All participants will be required to understand and agree with the study protocol. A delegated researcher or research coordinator will obtain written informed consent from all participants.

Participants under the following conditions or situations are ineligible: (1) survival expectancy of less than 3 months; (2) emergency operation, which was not scheduled in advance; (3) hypertension or hypotension that can significantly interfere with the study result; (4) diagnosis of arrhythmia, such as atrial fibrillation and frequent ventricular or supraventricular premature beats; (5) diagnosis of heart failure or valvular disease; (6) anemia with hemoglobin level <12 g/dL; (7) incapable of surgery due to hemodynamic or medical reasons other than stated above; (8) incapable of receiving acupuncture treatment on the determined location; (9) current use of gonadotropin-releasing hormone receptor agonists; (10) current use of drugs that may interfere with the result, including steroids, immunosuppressants, and drugs for psychiatric disorders; (11) significant comorbidities that may interfere with the interpretation of intervention efficacy or results, such as stroke, myocardial infarction, kidney disease, dementia, or epilepsy; (12) pregnant, planning to be pregnant within the study period, or breastfeeding; (13) previous participation in any other clinical trial within 1 month of participation, planning to participate in another clinical trial within 6 months after the enrollment date, or planning to participate in another clinical trial in the follow-up period; (14) failure to complete the informed consent form voluntarily; and (15) being deemed to be unsuitable for participation.

### Randomization and Allocation

Eligible participants who sign the informed consent form will be randomly assigned to the acupuncture or placebo group in a 1:1 ratio. Random sequences will be generated by permuted block randomization of block size 2 or 4 using the random allocation tool in R software 4.1 (R Foundation for Statistical Computing). Random sequence generation will be performed, and random sequences will be determined by an independent statistician prior to enrollment. Only the statistician who generates the random sequence will be aware of the full randomization sequence.

Each random sequence will be sealed in an opaque envelope and stored in a double-locked cabinet. The delegated researcher or research coordinator will explain the trial process to the candidate, obtain written informed consent, open the randomization envelope for each participant, and assign them to an appropriate group.

Intervention researchers will perform acupuncture or placebo acupuncture according to their assigned group. The intervention researchers will stay unblinded because the researchers will perform different interventions according to the group. However, the researchers will separate the person and location to maintain anonymization as robustly as possible. The participant, assessor, and statistician will be blinded, and the location where the intervention is performed will be separate from the location where the assessment will be performed. Interventions will be performed in the ward, and assessments will be performed in the operating room.

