Since the intervention will be conducted over a short period, strategies for study adherence have been deemed unnecessary. However, to improve adherence, follow-up surveys will be conducted both online and offline. The online platform data are only accessible to the principal investigator and the delegated research coordinator. Other data will be electronically locked or stored in a document archive accessible only to researchers for the duration of the study and for 3 years after its completion.

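### The person who takes consent also opens envelopes from blocks of 2 or 4 and can predict later allocations; separately, the safety-unblinding sentence must be reconciled with the statement that assessors stay blinded

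*Protocol article*

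**What the plan says.** **Allocation.** The protocol article (Randomization and Allocation) gives a delegated researcher or coordinator the whole chain: explain the trial, then "obtain written informed consent, open the randomization envelope for each participant, and assign them to an appropriate group". The sequence comes from "permuted block randomization of block size 2 or 4", prepared in advance by an independent statistician. The safeguards are that "Each random sequence will be sealed in an opaque envelope and stored in a double-locked cabinet" and that "Only the statistician who generates the random sequence will be aware of the full randomization sequence". Participant, assessor and statistician are listed as blinded and the acupuncturist as unblinded; the enrolling role appears in neither list.

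**Eligibility.** Study Process puts the eligibility evaluation after consent and before randomization. Eligibility contains criteria that call for judgement: abnormal blood pressure thought likely to disturb the results (the article gives no threshold), interfering comorbidity, and a catch-all for anyone considered unsuitable.

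**Unblinding.** Under Ethical Considerations, after a suspected unexpected serious adverse reaction, or when the DSMB suspects harm and asks for it, "the intervention researcher will unblind the allocation to other researchers and the committee, and submit the unblinded interim results". The limitations paragraph of the Discussion says, without exception, that outcome assessors remain blinded for the whole trial.

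**The concern.** A person who opens every envelope learns the sequence one entry at a time, whatever is said about who holds the full list. In short blocks the past says a good deal about the next entry, and the article publishes the block sizes while recruitment continues. If that person also influences who is approached or judged eligible, patients can be steered, knowingly or not, towards the arm expected next. The primary comparison is an unadjusted *t* test with 24 per arm, so a few selectively enrolled patients could matter. One discretionary exclusion concerns blood pressure, the very subject of the endpoint.

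The unblinding sentence raises a different risk. The anesthesiologists who assess outcomes also adjust remifentanil and desflurane. If they were among those told the allocations, their decisions could affect the endpoint even though the readings are automated.

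**Working it through.** The article gives no predictability figure to reproduce, so the check derives one.

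**Inputs from the article**
- One centre, so one run of envelopes: "prospective, single-center, randomized controlled clinical trial with a parallel-group design" (Study Design). No stratification is stated.
- Participants are "randomly assigned to the acupuncture or placebo group in a 1:1 ratio", in blocks of 2 or 4.
- 48 planned (Sample Size): 21/(1 − 0.10) = 23.3, rounded up to 24 per group; 2 × 24 = 48, as stated.
- 35 randomized by June 2025 (Results), leaving 48 − 35 = 13.

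**Assumptions**
- Sizes 2 and 4 are equally likely; the article gives no proportions.
- One person has seen all earlier allocations. That person guesses the arm that is behind and tosses a coin when the arms are level.

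**Step 1, all blocks of 2.** The first guess is right with probability 1/2 and the second is certain: (1/2 + 1)/2 = 75%.

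**Step 2, all blocks of 4.** By position:
- first 1/2;
- second 2/3, because two of the three remaining places belong to the other arm;
- third 1/3 × 1 + 2/3 × 1/2 = 2/3, because the first two are alike with probability 1/3 and the rest is then fixed;
- fourth 1.

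The sum is 2.833, and 2.833/4 = 70.8%.

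**Step 3, equal mix.** One block of each size holds 6 allocations, and (1.5 + 2.833)/6 = 72.2%. A simulation of 48 allocations gave 72.0% for this rule and 72.1% for an observer who also updates on the likely block size. Three of the 6 allocations are made when one arm leads by one; the guess is then right (1 + 2/3 + 1)/3 = 89% of the time.

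**Step 4, certain in advance (mix, current block size unknown).** Two like assignments at the start of a block reveal a block of 4 and fix both remaining places. This happens in 1/3 of blocks of 4: 2 × 1/3 = 0.667 certain allocations per 6, or 11%, about 5 of 48. The simulation also gave 11%.

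**Step 5, expected correct guesses**

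| Blocks | Rate | Of 48 | Of the last 13 |
|---|---|---|---|
| All 4 | 70.8% | 34.0 | 9.2 |
| Equal mix | 72.2% | 34.7 | 9.4 |
| All 2 | 75.0% | 36.0 | 9.8 |
| Past allocations unseen | 50% | 24.0 | 6.5 |

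**Step 6, would larger blocks do?** In a block of 2m the expected number of correct guesses is m − 1/2 + 2^(2m−1)/C(2m, m). This gives 2.833, 4.1 and 5.329 for sizes 4, 6 and 8. An equal mix gives (2.833 + 4.1 + 5.329)/18 = 68%, so larger blocks help little.

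**Step 7, the unblinding text.** No arithmetic applies. The sentence sets no limit to the affected participant, does not name or exclude the anesthesiologists or the analyst, and adds interim results, which go beyond one patient. Read that way, it cannot stand beside the Discussion's unqualified statement about assessors. A narrower reading, in which only the case concerned is opened, would remove most of the conflict, but the words do not settle it.

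**The case against.** **On allocation.** Envelopes are opaque, locked away and opened only after consent, so nobody learns the current patient's arm early. A reader might infer that allocation leaks to people who should not see it. The documents do not support that: someone has to open the envelope, and the enrolling role is not promised blinding. What remains is prediction of later allocations.

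The 72% is a worst case of its kind. The article allows for a researcher or a coordinator, so enrolment may be shared, and predictability falls if recruiters do not exchange what they have seen. The article does not say who decides eligibility. Most exclusions are diagnoses, drugs or a laboratory limit. A guessing rate is also not a bias in mmHg, and none can be derived here. All of this stands. The planned regression on ward and preoperative blood pressure and anxiety would reduce measured imbalance but not remove selection on other features, and the primary test is unadjusted.

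**On assessment.** A reader might also infer assessment bias from the envelope step. That does not follow. Blood pressure is read automatically every 2.5 minutes, and separate anesthesiologists assess it away from the ward. Nor does the data-access rule ("The online platform data are only accessible to the principal investigator and the delegated research coordinator") show such bias: the questionnaires are completed by blinded participants, and the coordinator is not said to score anything.

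**On unblinding.** The sentence is ambiguous. The allocation may mean that of the one case, the DSMB's request may govern both triggers, and DSMB operation is referred to procedures not shown. Adverse events so far are reported as mild and unrelated, and no use of the clause is reported. So it cannot be said that assessors or the analyst will be unblinded, only that the text permits it.

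**Conclusion.** Both points hold in limited form.

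- **Prediction.** The recruiter can predict later allocations: about 72% correct (71% to 75% across the possible block mixes) against 50% by chance, with about 11% certain in advance. This rests on equal use of the two block sizes and on one person seeing every earlier allocation. Selection bias further requires that this person has some say in who is approached or found eligible. It is a risk in the procedure; nothing in the article shows that it has occurred.
- **Unblinding.** The Ethical Considerations and Discussion texts conflict on a literal reading and must be reconciled. The risk is conditional on the clause being triggered and on assessors being among the recipients.

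Neither point invalidates the trial, and both are cheap to put right.

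**What to change.** **Allocation, for the remaining enrolments (13 as of June 2025)**
1. The coordinator logs consent, eligibility and baseline questionnaires so that they cannot be changed afterwards.
2. Only then, at V1, the acupuncturist opens the next numbered envelope and does not tell the coordinator the arm.
3. The acupuncturist takes no part in recruitment or eligibility decisions. This condition matters because the same person delivers both treatments. Under the present plan that person learns every arm anyway, so no one new is unblinded.

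If the arm is neither shared nor inferred, the recruiter's guess returns to about 50% for allocations not already seen. Role separation, rather than larger blocks, is the effective change.

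**Unblinding.** Rewrite the Ethical Considerations sentence to agree with the Discussion:
- for a single case, unblind only the affected participant, to named recipients (the DSMB and the authority);
- any unblinded interim tables go from the independent statistician to the DSMB alone;
- the anesthesiologists and other assessors, and the analysis statistician, stay blinded.

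**Cost.** A short procedural amendment with existing staff, and slightly less convenient envelope handling on the ward. It does nothing for the 35 participants already randomized.

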### Intervention

Acupuncture will be performed with a disposable, sterilized, stainless steel needle measuring 0.20 × 30 mm (Dongbang Medical) in both groups. Ten acupoints (PC6, PC5, SP3, KI3, and ST36) will be chosen bilaterally for the intervention group (acupuncture group). The depth of acupuncture varies (1 to 1.5 cm) among the participants. After acupuncture needles are inserted, they will be manually manipulated to obtain a predetermined sensation, De Qi. Acupoints PC6 and PC5 will be inserted with depth adjustment to reach the anatomical plane right above the median nerve, thereby facilitating a more prominent sensation. Acupuncture will continue for 20 minutes. Ten other points that are not official acupoints and are not on the median or peroneal nerve will be chosen for the placebo group. An acupuncture needle depth of 0.5 cm will be used.

Acupuncture or placebo will be administered 2 times during the first and second visits. Administration will be done by a qualified acupuncturist who is a physician in Korean medicine with 10 years of clinical experience, independent of the anesthesia team.

### Study Process

After a sufficient explanation of the purpose and methods of this clinical study by a researcher, subjects who voluntarily decide to participate and sign a written consent form will be evaluated for eligibility at the screening visit. Eligible subjects will be randomly assigned to the acupuncture or placebo control group according to randomization. Acupuncture treatment will be performed twice, one day before surgery (V1) and on the day of surgery (V2).

All intraoperative management and outcome assessments will be independently performed by anesthesiologists who are not involved in the acupuncture procedure. All participants will fast for 6-8 hours prior to surgery. After entering the operating room (V3), electrocardiography, pulse oximetry, and monitoring of the partial pressure of end-tidal carbon dioxide (IntelliVue MX550; Phillips North America Corporation) will be performed continuously. Automated oscillometric measurements of blood pressure at 2.5-minute intervals and “train of four” (TOF) (ToFscan; Drager Technologies) assessments will also be performed. Throughout the surgery, these data will be downloaded to personal computers using RS232C cables.

After checking the initial vital signs (heart rate, blood pressure, and oxygen saturation) (P1), anesthesia will be induced intravenously with propofol (1-2.5 mg/kg) and remifentanyl (0.01-0.1 ng/kg/min). Mask ventilation (P2) with desflurane will be performed after the administration of rocuronium (0.6-1 mg/kg). Once the TOF ratio reaches <2, the anesthesiologist will perform tracheal intubation (P3). The lungs of the subjects will then be ventilated with desflurane and oxygen in air (FiO2=0.5), and the tidal volume and ventilation rate will be adjusted to maintain the partial pressure of end-tidal carbon dioxide between 35 and 45 mmHg. An additional venous tube will then be secured (P4).

With the patient in the lithotomy position and under general anesthesia, the abdomen will be prepared, painted, and draped in the usual manner (P5). The uterine elevator will be inserted. A skin incision will be made (P6), and a trocar will be inserted. CO_2_ gas will be infused to create a pneumoperitoneum at a pressure of 12 mmHg (P7). After entering the abdominal cavity, the patient’s position will be changed to the Trendelenburg position. The pelvic cavity and the entire abdomen will then be examined. The bilateral pelvic sidewall triangles will be opened parallel to the infundibulopelvic ligament, and ureteral dissection will be performed. The ureteral course will be identified, and the right round and ovarian ligaments will be coagulated with a bipolar endocoagulator and cut with endoscissors. The left uterine ligament will be manipulated using the method described above. The bladder flap will be pushed, and the posterior broad ligament will be mobilized. The bilateral uterine vessels will be skeletonized, coagulated, and cut. Circumferential colpotomy will be performed by using unipolar scissors. The uterus will be removed transvaginally, and the vaginal cuff will be closed using continuous intracorporeal sutures. Hemostasis and ureteral peristalsis will be ensured, and the abdominal cavity will be irrigated with normal saline. The subcutaneous tissue and skin will be closed layer by layer.

During the procedure, the infusion rate of remifentanil and the concentration of desflurane (6.0-7.0 vol%) will be adjusted to maintain stable hemodynamic values (systolic blood pressure >80 mmHg; heart rate >45 beats/min) and an appropriate depth of anesthesia (>1 minimal alveolar concentration). If necessary, ephedrine or atropine will be administered to maintain stable hemodynamic values. All decisions will be made by a qualified anesthesiologist with at least 10 years of clinical experience.

The neuromuscular blockade will be reversed by administering sugammadex (2-5 mg/kg) at the end of the surgery, and the patient will be confirmed to be fully awake (TOF >0.9) and transferred to the postanesthetic care unit (P8).

By participating in this clinical study, the study participants will not be restricted from receiving rescue medicine required in the surgical process. If rescue medicine or rescue treatment is administered, the researcher will record the combination of therapy and rescue medicine in a case report form.

Since the intervention will be conducted over a short period, strategies for study adherence have been deemed unnecessary. However, to improve adherence, follow-up surveys will be conducted both online and offline. The online platform data are only accessible to the principal investigator and the delegated research coordinator. Other data will be electronically locked or stored in a document archive accessible only to researchers for the duration of the study and for 3 years after its completion.

